# **STUDY OBJECTIVES**

## **2.1 OBJECTIVES**

### **2.1.1 Primary Objective**

##### To establish the feasibility and reproducibility of novel MR imaging techniques in the evaluation of treatment response in women with uterine leiomyomas (fibroids).

### **2.1.2 Secondary Objectives**

To provide mechanistic information on whether the reduction in blood flow of uterine/fibroid vasculature in shrinkage fibroids is dependent upon subjects being hypoestrogenic.

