## **2.2 ENDPOINTS**

### **2.2.1 Primary Endpoint**

Feasibility and reproducibility of use of structural, dynamic contrast and magnetization transfer (MTI) MR imaging to visualize and quantify changes in:

1. Uterus and fibroid volume

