**3.1.2 Measurements:**

Comparisons will be made between the following imaging modalities:

1. Sonographic assessment, colour Doppler imaging.
2. 1.5T MR imaging, including structural, dynamic contrast and magnetization transfer imaging.
3. Ex-vivo imaging with 7T MR scanner correlated with uterine histo-morphology.

For imaging exercises there will be one record per patient for each measurement at each time-point. The largest fibroid will be selected and total uterine volume measured.

It is not possible to have patients “blinded” to treatment option. It will be possible for the statistician, pathologists, radiologists, technicians and non clinical staff to be “blinded” to the treatment allocation, to the results of previous time-points, and to the results of other measures at the same time-point.

Following successful screening procedures all the participants will have a further 5 visits to the RIE.

On each of the visits 1 to 4 every participant will have a MRI, Ultrasound and Doppler. If Visit 1 falls within 28days of screening then the screening scan will remain valid. If this is anticipated then Dopplers will be carried out at screening.

Visit 1 will be carried out prior to randomisation (Within 28 days of Day 1)

Visit 2 at 14 days+/- 3 days following commencement of treatment

Visit 3 at 28 days+/- 3 days following commencement of treatment

Visit 4 Within 10 days prior to scheduled hysterectomy

Visit 5 Day of Hysterectomy and Ex-vivo imaging with 7T MR scanner of uterus

Blood samples will be taken on 3 occasions - at Screening, Day 28+/- 3 days (Visit 3)and on the day of Hysterectomy (Visit 5) to assess Urea and Electrolytes (U&E's), Full Blood Count (FBC), and Liver Function Tests (LFT's). These blood samples will be taken on scheduled study visits to the hospital.

A 10ml blood sample will be obtained on 11 occasions (Group 2) and 10 occasions (Groups 1 & 3) to obtain an estimate of Oestradiol (E), Progesterone(P), Luteinising Hormone (LH) and Follicle Stimulating Hormone (FSH). A small aliquot of blood will be stored in the freezer in reserve in case of any laboratory processing difficulties.

Some of these blood samples will be taken at the RIE when they coincide with Scheduled Study Visits. The participants will be given the option to have the rest of the blood samples taken in their own home if this is more convenient to them.

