### Subsequent scans (TVU / TAS) will be performed following start of medication at Visits 2, 3 and 4 (main study), Day 28+/- 3 days (Pilot Group A) and prior to hysterectomy (Pilot Groups A, B & C).and the same measurements will be carried out to record any changes from baseline.

## **7.2.2 Colour Doppler imaging**

To determine blood flow of the main uterine arteries colour Doppler imaging will be performed prior to the first study drug dose and repeated following start of medication at Visits 2, 3 and 4 (main study), Day 28+/- 3 days (Pilot Group A) and prior to hysterectomy (Pilot Groups A, B & C). Blood flow will be expressed using two impedance indices: the resistance index (RI) and the pulsatility index (PI). For each impedance index, the average of three measurements will be taken from the left and right arteries, respectively to enhance reproducibility.

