**Primary analyses will be:**
(1) the comparison of the pre-hysterectomy uterine volume between the treated and control groups using t-test or a non-parametric equivalent as appropriate.:

(2) Bland-Altman analyses comparing the pre-hysterectomy MR with USS.

**Secondary analyses**: We will perform similar analyses for uterine vascular perfusion. A variety of other exploratory analyses will be performed including examining changes over time, and quality of images. Data will also be considered in the context of the patient’s hormone profile over the time of the study (taken from blood and urine samples).

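### MR reproducibility is the primary objective, but the only named agreement analysis is MR against ultrasound and no repeat MR scan or reading is provided for, so it is not estimated

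*Protocol*

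**What the plan says.** - Section 2.1.1 gives the primary objective: "To establish the feasibility and reproducibility of novel MR imaging techniques in the evaluation of treatment response".
- Section 2.2.1 gives the primary endpoint as "Feasibility and reproducibility of use of structural, dynamic contrast and magnetization transfer (MTI) MR imaging to visualize and quantify changes in" uterus and fibroid volume. The note to Section 2.2.2 adds that no efficacy measurement is required.
- Section 3.1.2 states that "there will be one record per patient for each measurement at each time-point".
- Section 9.2 names two primary analyses: a comparison of pre-hysterectomy uterine volume between treated and control groups, and "Bland-Altman analyses comparing the pre-hysterectomy MR with USS". For the secondary analyses it says "We will perform similar analyses for uterine vascular perfusion". Changes over time and image quality are listed as exploratory.
- Section 9.1 states that 30 subjects give limits of agreement to within 0.6 SD of the difference between measurements.
- Ultrasound volume is an ellipsoid estimate from three diameters (Section 7.2.1). MR volume comes from the structural scans (Section 7.2.3).
- The only replicate readings in the protocol are three Doppler measurements per artery, which are averaged (Section 7.2.2).

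**The concern.** Reproducibility is how closely a method agrees with itself when it is repeated. Estimating it requires at least two MR results on the same woman under conditions where the true value has not changed. Neither primary analysis uses such a pair. The first compares groups, and the second compares two different methods at one visit. The endpoint also concerns measuring change, whereas the agreement analysis is cross-sectional.

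If the plan is followed as written, the trial ends with no within-method SD and no repeatability coefficient for MR volume, for the dynamic contrast measures or for the magnetisation transfer ratio. A later trial wishing to use MR as a response biomarker would not know how large a change in one woman exceeds MR measurement noise.

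**Working it through.** **1. The plan's own figure.** For n = 30, the 95% CI half-width of a limit of agreement is 1.96 × √(3/n) = 1.96 × √(3/30) = 0.62 SD of the difference. The fuller variance gives 1.96 × √(1/30 + 1.96²/58) = 0.62. The stated 0.6 reproduces. The difference to which it applies in Section 9.2 is MR minus ultrasound.

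**2. What that difference contains.** With one record per method,

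Var(MR − USS) = Var(MR error) + Var(USS error) + Var(method-by-subject),

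taking the errors as independent. One variance is observed and up to three components are unknown.

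**3. What it implies for MR.** The repeatability coefficient is 1.96 × √2 × SD(MR error) = 2.77 × SD(MR error). If MR error is a share f of the variance of the difference, the coefficient is 2.77 × √f × SD of the difference.

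| Share f due to MR | MR repeatability coefficient, in SDs of the difference |
| --- | --- |
| 0 | 0 |
| 0.25 | 1.39 |
| 0.50 | 1.96 |
| 0.75 | 2.40 |
| 1 | 2.77 |

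The planned data cannot place f anywhere in this range.

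**4. Illustration in cm³.** The protocol gives no SD for the MR-ultrasound difference, so 40 cm³ is assumed, with no method-by-subject term.

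- MR error 10, USS error 38.7: √(10² + 38.7²) = 40, and the MR repeatability coefficient is 2.77 × 10 ≈ 28 cm³.
- MR error 38.7, USS error 10: the SD of the difference is again 40, and the coefficient is 2.77 × 38.7 ≈ 107 cm³.

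The limits of agreement are equally wide in both cases (1.96 × 40 = 78 cm³ either side of the mean difference). Against the 160 cm³ difference in change used in Section 9.1, the two coefficients are 28/160 = 17% and 107/160 = 67%.

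**5. What a second reading would give.** For n scans (one per woman) each read twice, SD(within) = √(Σd²/2n) on n df. The 95% CI multipliers are √(n/χ²) at the 97.5% and 2.5% points.

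| Scans read twice | 95% CI, as a multiple of the estimate |
| --- | --- |
| 10 | 0.70 to 1.75 |
| 15 | 0.74 to 1.55 |
| 30 | 0.80 to 1.34 |

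**6. What the control arm already offers.** Ten untreated women with four MRIs each, after removing visit means, give (10 − 1) × (4 − 1) = 27 df. The CI multipliers are 0.79 and 1.36. This assumes that all ten complete all four scans.

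**The case against.** Several points on the other side have force.

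- *The one-record rule.* A reader might infer that Section 3.1.2 forbids repeat readings. The text does not go that far. Section 7.2.2 takes three Doppler readings and averages them, so one record can coexist with several readings, and the sentence may be only a data-capture rule. Repeat MR readings are not provided for, which is different from being banned. A statistical analysis plan, not available here, could add re-reading of stored images. It could not create same-occasion repeat scans.
- *Perfusion.* A reader might infer that Bland-Altman limits are planned between MR perfusion and Doppler. Section 9.2 does not say so, and the similar analyses it mentions could mean the group comparison alone. If Bland-Altman were meant, it would fail: the resistance and pulsatility indices of the uterine arteries and the fibroid-to-myometrium signal ratio are different quantities. The wording needs clarifying, but it is not a demonstrated error.
- *Ultrasound as the main culprit.* A reader might infer that ultrasound supplies most of the disagreement and that MR would be unfairly judged poor. The documents give no error SD for either method and set no acceptance limit for agreement, so neither claim is supported.
- *Existing repeats.* The controls have serial MRIs, but these are weeks apart and carry biological and cycle variation. Section 9.2 treats changes over time only as exploratory. Pilot Group C has two scans in up to 5 women, but at 1.5T and 3T and with no stated analysis.
- *Hypothesis-generating study.* Section 9.1 says so. That excuses wide intervals. It does not excuse having no estimate for the primary endpoint.

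The mismatch between the primary objective and the primary analysis survives all of these.

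**Conclusion.** The concern holds for the reproducibility half of the objective. Feasibility is a separate matter and is touched by the exploratory review of image quality. The two primary analyses, together with the absence of any same-scanner repeat scan or repeat reading, leave MR reproducibility unestimated. From the planned data the MR repeatability coefficient is bounded only between 0 and 2.77 SDs of the MR-ultrasound difference. That bound assumes independent errors, and the cm³ figures rest on an assumed SD of 40. The arithmetic behind the stated 0.6 SD is sound, but it does not give precision for MR reproducibility.

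This is worth correcting before analysis because it concerns the primary endpoint. Reader error can still be recovered if the images are kept. Scan-rescan error cannot be isolated without repeat scanning.

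**What to change.** 1. **Primary reproducibility analysis (Section 9.2).** Specify the within-subject SD and repeatability coefficient for log volume, magnetisation transfer ratio and an MR perfusion index. Take them from a blinded second reading by the existing reader of a defined set of stored MR scans. State in Section 3.1.2 that both readings are kept. This yields intra-reader error only, and the table in the working shows the precision for different set sizes.
2. **Control-arm serial MRIs.** Add the within-woman SD from the untreated controls' four scans, reported as an upper bound on MR error because it includes biological and cycle variation. First reconcile the timing of control-arm Visit 3: Section 3.1.2 counts 28 days from the start of treatment, while the control table in Appendix 4 counts 28 days from Visit 2, which is about day 14 + 28 = 42.
3. **MR versus ultrasound.** Relabel it as between-method agreement and use the same-visit pairs from Visits 2 to 4 (at most 3 × 30 = 90) in a repeated-measures Bland-Altman model. Any agreement on change from Visit 1 must note that Section 3.1.2 lets the screening ultrasound stand in for Visit 1 when the two fall within 28 days, so the baseline MR and ultrasound may not be contemporaneous.
4. **Perfusion.** Clarify that the similar analyses do not include Bland-Altman limits between MR signal ratios and Doppler indices. If the two are compared, use the correlation of within-woman changes.

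The cost is some hours of the existing reader's time and a protocol amendment, which under Section 14.1 needs ethics, regulatory and R&D approval. No extra scans or staff are required. The remaining gaps are inter-reader error and a separate scan-rescan component, which should be stated as limitations.

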# **ADVERSE EVENTS**

The Investigator is responsible for the detection and documentation of events meeting the criteria and definitions detailed below.

Full details of contraindications and side effects that have been reported following administration of the trial drug can be found in the relevant Summary of Product Characteristics (SoPC) in Appendix 1.

Participants should be instructed to contact their Investigator at any time after consenting to join the trial if any symptoms develop. All adverse events (AEs) that occur after joining the trial must be reported in detail in the CRF. In the case of an AE, the Investigator should initiate the appropriate treatment according to their medical judgment. Participants with AEs present at the last visit must be followed up until resolution of the event.

Any abnormal measurement/finding from any of our clinical interventions (eg patient observations, urine, blood, imaging) will be dealt with appropriately in a standard clinical way.

Any complications which arise at or after hysterectomy-excess blood loss, post operative pyrexia/infection, damage to bladder/bowel or deep vein thrombosis will not be recorded as adverse events within this study. These are recognised complications of hysterectomy which are discussed routinely between the surgeon and the patient when the operation consent form is completed.

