### aged >18 years.

### Scheduled for hysterectomy with a fibroid uterus

### At least one intramural non-pedunculated, submucosal or subserous fibroid with a diameter of  2cm or multiple small fibroids with a uterine volume of  200cm3 confirmed by transvaginal or abdominal ultrasonography

### Normal cervical cytology within 3 years.

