## **10.1 DEFINITIONS**

An **adverse event** (AE) is any untoward medical occurrence in a clinical trial subject who is administered a medicinal product, which does not have a causal relationship with the treatment.

An **adverse reaction** (AR) is any untoward or unintended response to an investigational medicinal product related to any dose administered.

An **unexpected adverse reaction** (UAR) is an adverse reaction that is not consistent with the product information in the SoPC.

A **serious adverse event** (SAE), **serious adverse reaction** (SAR) or **suspected unexpected serious adverse reaction** (SUSAR) is any AE, AR or UAR that at any dose:

- results in death;
- is life threatening (i.e. the subject was at risk of death at the time of the event; it does not refer to an event which hypothetically might have caused death if it were more severe);
- requires hospitalisation or prolongation of existing hospitalisation;
- results in persistent or significant disability or incapacity;
- is a congenital anomaly or birth defect.

Note: Hospitalisations for treatment planned prior to randomisation and hospitalisation for elective treatment of a pre-existing condition will not be considered as an AE. Complications occurring during such hospitalisation will be AEs.

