## **10.2 DETECTING AEs AND SAEs**

All AEs and SAEs must be recorded from the time a participant consents to join the study until the last study visit.

The Investigator should ask about the occurrence of AEs/SAEs at every visit during the study. Open-ended and non-leading verbal questioning of the participant should be used to enquire about AE/SAE occurrence. Participants should also be asked if they have been admitted to hospital, had any accidents, used any new medicines or changed concomitant medication regimens. If there is any doubt as to whether a clinical observation is an AE, the event should be recorded.

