### **Assessment of Causality**

The Investigator must make an assessment of whether the AE/SAE is likely to be related to treatment according to the following definitions. All AEs/SAEs judged as having a reasonable suspected causal relationship (e.g. possibly, probably, definitely) to the study drug will be considered as ARs/SARs. If concomitant or rescue/escape drugs are given, the Investigator must also make an assessment of whether the AE/SAE is likely to be related to an interaction between the study drug and concomitant or rescue/escape drugs or whether the AE/SAE might be linked to either the study drug or concomitant or rescue/escape drugs but cannotbe attributed to onlyone of these drugs. All AEs/SAEs judged as being related (e.g. possibly, probably, definitely) to an interaction between the study drug and concomitant or rescue/escape drugs, or any AE/SAE that cannot be attributed to only the study drug or the concomitant or rescue/escape drugs will also be considered to be ARs/SARs .

**Unrelated**: where an event is not considered to be related to the study drug.

**Possibly**: although a relationship to the study drug cannot be completely ruled out, the nature of the event, the underlying disease, concomitant medication or temporal relationship make other explanations possible.

**Probably**: the temporal relationship and absence of a more likely explanation suggest the event could be related to the study drug.

**Definitely**: The known effects of the study drug or its therapeutic class, or based on challenge testing, suggest that study drug is the most likely cause.

Alternative causes such as natural history of the underlying disease, concomitant therapy, other risk factors and the temporal relationship of the event to the treatment should be considered and investigated. The blind should not be broken for the purpose of making this assessment.

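### Section 10 bars recording of surgical complications that Section 10.1 calls adverse events, and 10.1's own definition of an adverse event leaves out drug-related ones

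*Protocol*

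**What the plan says.** The opening of Protocol Section 10 names four kinds of complication at or after hysterectomy: excess bleeding, post-operative fever or infection, bladder or bowel damage, and deep vein thrombosis. It states that these "will not be recorded as adverse events within this study", on the ground that they are known risks discussed when the operation is consented.

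The note closing Section 10.1 reads "Hospitalisations for treatment planned prior to randomisation and hospitalisation for elective treatment of a pre-existing condition will not be considered as an AE", and continues: "Complications occurring during such hospitalisation will be AEs". Section 10.2 sets the window: "All AEs and SAEs must be recorded from the time a participant consents to join the study until the last study visit". In Section 3.1.2 the last main-study visit (Visit 5) is the day of hysterectomy, and Appendix 4 ends every pilot group at the operation too. Appendix 4 ticks the adverse event column at that visit in all six groups.

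On the definition, Section 10.1 describes an adverse event as an untoward occurrence in a subject given a medicinal product, "which does not have a causal relationship with the treatment". Section 10.4.2 then says "All AEs/SAEs judged as having a reasonable suspected causal relationship" to the study drug are to be treated as adverse reactions.

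**The concern.** Two people following different paragraphs of the same section would complete different forms for the same event. The exclusion in Section 10 also makes no exception for serious events. Bowel damage that lengthens the hospital stay meets the seriousness criteria in 10.1 and would have to reach the trials unit within 24 hours under 10.5. Under Section 10 it is not written down at all. An unrecorded event cannot go through the causality assessment in 10.4.2 or the expectedness assessment in 10.4.4, so it could never be identified as a suspected unexpected serious reaction for 10.6. There is no data monitoring committee or steering committee to notice the gap (Sections 12.4 and 12.5). The monitoring plan in Appendix 2 has adverse events checked against source, but a monitor cannot verify against two opposite rules.

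The definition raises a separate difficulty. If an adverse event is by definition unrelated to treatment, an investigator cannot sort adverse events into related and unrelated.

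**Working it through.** No figure in the plan is at issue, so the check sets the texts against each other.

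**Do the two rules cover the same events?**

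1. The 10.1 note applies to admissions planned before randomisation or for elective treatment of an existing condition.
2. An inclusion criterion in Section 4.2 is "Scheduled for hysterectomy with a fibroid uterus". The first limb of the note therefore covers the 30 randomised women. The second limb covers the pilot women, who are not randomised.
3. Complications during the hysterectomy admission are thus adverse events under 10.1 for everyone: 30 + 35 = 65 women at full recruitment.
4. Section 10 bars the listed complications for the same 65. Neither paragraph is said to override the other.

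**Which events are in dispute?**

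| Event | Section 10 | 10.1 note | 10.2 window |
| --- | --- | --- | --- |
| Listed complication, day of surgery | not recorded | adverse event | inside |
| Listed complication, later in the same admission | not recorded | adverse event | arguably closed |
| Listed complication, after discharge | not recorded | silent | closed |

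The clear conflict is the first row. The second row shows that the window itself needs stating.

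**Is causality a live question on the day of surgery?** In Groups 1 and 2, surgery falls 21 to 28 days after the last goserelin depot, and depots are given every 28 ± 3 days. Surgery therefore falls within about one dosing interval of the last dose. Calling an event a known risk of surgery does not answer whether the drug contributed.

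**What does the definition lose if read literally?**

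1. Related events are not adverse events (10.1). They fall under the separate definition of an adverse reaction.
2. The definition of serious events in 10.1 spans adverse events and reactions alike, so a serious drug reaction is still caught.
3. The recording rule in 10.2 names only adverse events and serious adverse events. What is left without a recording instruction is the non-serious drug reaction.

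**Illustration of scale (assumed rates).** The documents give no complication rate. Suppose a chance p of 5% to 30% per woman of a listed complication arising by the last visit. Over the 30 randomised women the expected number is 30p, that is 1.5 to 9. The chance of at least one is 1 − (1 − p)^30: 1 − 0.95^30 = 0.785 at the low end and above 0.99 at the high end. All of these would be absent from the data under Section 10 and present under 10.1.

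**The case against.** The best case for the protocol is that the intent is clear enough. Section 10 gives a reason for its exclusion. The separate definition of an adverse reaction, the causality step, and the instruction in 10.2 to record whenever in doubt all show that drug-related events were meant to be captured. The missing word 'necessarily' is the plain cause of the faulty definition. This stands: the definition is chiefly a drafting error and probably loses little data. It does not rescue the first point, because the rule on doubtful cases cannot override an explicit prohibition.

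It is also fair that recording closes at the last visit, so an infection or thrombosis arising after discharge falls outside the window whichever paragraph governs. The dispute does not extend to every peri-operative complication.

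A reader might infer that the literal definition also excludes every event in the untreated groups, since it speaks of a subject given a medicinal product. The documents do not support that. The wording is not limited to the investigational product. Controls and Pilot Groups B and C are scheduled for gadolinium (Appendix 4), and Section 5.3 says Buscopan is routine at pelvic MRI. Only the time between consent and the first scan is arguable, and that applies to every group alike.

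**Conclusion.** The point holds as two internal faults. First, Sections 10 and 10.1 give opposite orders for listed complications arising by the last study visit, at up to 65 operations, and following Section 10 would leave even a serious surgery-day event unrecorded and unassessed. Second, the adverse event definition contradicts the causality step and, taken literally, leaves non-serious drug reactions without a recording rule.

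The harm is incomplete safety data. A reader might go further and infer biased safety comparisons between arms, or the loss of a comparison of surgical benefit or harm. Neither follows. The exclusion applies equally to all groups, no planned analysis uses operative outcomes, and Section 2.2.2 says no efficacy measurement of the drug options is required. Nor does the use of cetrorelix outside its licensed indication add much: it is given only in Group 2, with the last dose around day 7 of a course of about 13 weeks.

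The conclusion rests on the text alone. The assumed complication rates illustrate scale and nothing depends on them.

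**What to change.** Reconcile Section 10 and the 10.1 note into a single rule. Complications arising up to the last study visit are recorded in all groups and assessed against the seriousness criteria in 10.1. State whether the window closes on the day of surgery or at the end of the admission. If the aim of the exclusion was to limit workload, recognised surgical complications can be listed as expected and exempted from expedited reporting while still being recorded.

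Change the 10.1 definition so that an adverse event does not *necessarily* have a causal relationship with treatment, and apply it to all consented participants so that it matches the window in 10.2.

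The cost is two wording corrections and a few more adverse event forms. The change affects recording only, not the care of participants.
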